### Blinding and limitation of risk of bias

Given the nature of the study and intervention procedures, blinding is not possible for study staff nor participants. The principal investigators, co-investigators, and statistician will remain blinded to the study arm allocation of participants through the course of fieldwork and primary outcome analysis.

### Data collection and management

Clinic and study staff will enter data directly onto encrypted, password-protected study tablets at the eight participating study clinics. We have developed standard operating procedures for data collection, management, and quality assurance that will be implemented systematically across all study sites. We designed electronic data collection forms to provide clear instructions and to have automated systems to ensure correct study procedures. For example, local RAs will not be able to access the baseline survey until an eligible screening survey and informed consent have been documented. The electronic data forms also have real-time range checks and skip patterns driven by internal logic to minimize missing or incorrect data. To ensure data integrity, regular quality assurance measures will be performed by data officers in Kenya, Uganda, and the USA to assess for missing, incomplete, or invalid data fields. Study tablet data will be synced and backed up centrally to secure servers in Kenya and Uganda daily and uploaded to secure servers at the University of California, San Francisco (UCSF).

### Statistical analysis

For the primary outcome of HIV retesting, we will estimate a logistic regression model to determine the effect of each behavioral intervention. The main predictors in our regression model will be indicator variables for each intervention group, with the reference being the control group. We will also include study site fixed effects to account for variation between study sites in HIV retesting. While the inclusion of site fixed effects can reduce power by consuming degrees of freedom, it can also increase precision when there is substantial variation in retesting rates across sites. Given the number of intervention groups, we will account for multiple hypothesis testing by using the Benjamini and Hochberg Procedure to control the false discovery rate [41].

For secondary analyses, we will determine the effect of the interventions relative to control on PrEP uptake (i.e., acceptance of referral to PrEP) at time of retesting HIV-negative by estimating a logistic regression model where the dependent outcome is PrEP uptake, with the model including fixed effects for study community and adjusting for multiple comparisons as described for the primary outcome. We will conduct similar analyses with logistic regression models for the dependent outcomes of HIV seroconversion among participants who retest and linkage to HIV care and ART initiation among those who test HIV-positive. We will report the proportion of participants who retest HIV antibody-positive by study arm and overall, as well as the proportion who link to HIV care and start ART among persons who seroconvert. Although we will be underpowered to detect differences between study arms in HIV-positivity and linkage to care, we will be able to describe these important outcomes among a large sample of adults at risk of HIV exposure and we will identify baseline characteristics that are associated with incident HIV infection using logistic regression models.

Following completion of the study, we will use trial data to examine which interventions are most effective in increasing HIV retesting among three pre-specified subgroups of interest (men aged > 25 years, young women aged 15–24 years, and those reporting > 1 sexual partner in the past 3 months at baseline), given their higher risk of HIV exposure. For standard subgroup analyses, we will examine the effects of each intervention among the three pre-specified subgroups. Heterogeneous effects in subgroups will be estimated using logistic regression models that include interaction terms between indicators of intervention group and subgroup. The results of these analyses will enable us to identify which interventions are most effective in each of the three subgroups and to conduct classical tests for heterogeneity. Restricting our analyses to three pre-specified subgroups will preclude the discovery of large but unexpected treatment effect heterogeneity. To address this challenge in ways that do not spuriously identify treatment effect heterogeneity, we will use machine learning (ML) methods [42–48] to flexibly discover heterogeneous treatment effects across a large set of subgroups that are not specified a priori and are defined by a combination of individual and community characteristics. We will further estimate the potential benefit of using ML-based intervention targeting to improve outcomes, relative to one-size-fits-all or simpler (e.g., subgroup-based) targeting strategies [49].

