#### Random allocation

After eligibility is determined and the baseline questionnaire is completed, enrolled participants will be randomized to one of the 12 study arms using parallel group randomization, stratified by sex and by study site, using a computer-generated sequence with permuted blocks of size 36. Study arm allocation will be revealed to participants and research assistants (RA) on the study tablet, which will display a digital rotating wheel. Participants may choose when to stop the wheel’s rotation by clicking or requesting the RA to click a “stop” button, which will then reveal the randomization study arm assignment within the relevant stratum. The data analyst generated these random allocation sequences in advance, and RAs who assign participants to the interventions will not have access to the random allocation sequence.

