### Sample size

We made the following assumptions in determining the sample size and minimum detectable effect sizes. With 64,000 adults (≥ 15 years) testing for HIV in 2023 at the eight study HIV testing service sites and a reported HIV positivity of ~ 2%, we estimate there are about 62,700 HIV-negative adults tested per year in these study communities. We estimate that about 50% of adults (about 31,000/year) accessing HIV testing at HIV clinic sites will be classified as being at increased risk of HIV infection based on their self-reported answers to risk screening questions and thus will require quarterly HIV retesting. Based on our prior HIV retesting studies in Uganda, we anticipate at least 90% of eligible adults will agree to participate in the megatrial [29, 32]. With enrollment over 18–24 months, we anticipate enrolling 30,000–40,000 participants in the trial, with a range of 2500–3333 participants per arm in a 12-arm trial.

Based on our previous retesting study in Uganda, we assumed that 38% of the control group will retest for HIV within 6 months [29]). With a sample size of at least 3000 participants/arm, we will have 80% power to detect a 4.7 percentage-point difference in HIV testing for any of the intervention groups compared to the control group. These power calculations account for multiple hypothesis testing by using a Bonferroni correction and setting the significance level to 0.00455 (i.e., 0.05/11 comparisons between interventions and control). This is a very conservative approach; however, since we will have more statistical power in our analyses by using the Benjamini and Hochberg Procedure to control the false discovery rate [41] and covariate adjustment will also improve efficiency. Thus, in practice we expect to be able to detect differences between each intervention group and the control group that are smaller than 4.7%.

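### Randomisation is stratified by sex and site, but the stated primary model adjusts for site only; adding sex is a free, modest improvement

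*Protocol article*

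**What the plan says.** Random allocation (protocol article): participants are allocated to 12 arms "stratified by sex and by study site, using a computer-generated sequence with permuted blocks of size 36".

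Statistical analysis: the primary analysis is a logistic regression. "The main predictors in our regression model will be indicator variables for each intervention group, with the reference being the control group". The adjustment terms follow: "We will also include study site fixed effects to account for variation between study sites in HIV retesting". The section weighs what site terms may cost and gain in power and does not mention sex. The PrEP-referral model likewise names fixed effects for study community only, and the seroconversion, linkage and ART models are described as similar.

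Sample size: "we will have 80% power to detect a 4.7 percentage-point difference in HIV testing", at a Bonferroni level of 0.05/11 = 0.00455. The section then gives two reasons why this is conservative. The first is that Benjamini-Hochberg will be used in the analysis. The second is that "covariate adjustment will also improve efficiency". It concludes that "in practice we expect to be able to detect differences between each intervention group and the control group that are smaller than 4.7" percent.

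**The concern.** The analysis should normally reflect the way the trial was randomised. Permuted blocks within sex-by-site strata force the arms to be nearly equal in sex composition, so differences in retesting between men and women add almost nothing to the true variability of an arm-versus-control contrast. A model without sex does not know this and still treats that variation as noise. If sex predicts retesting, the test is a little too cautious.

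This is not a detail left unstated. The article writes out a primary model and includes one of the two stratification factors. The sponsor also treats sex as relevant elsewhere: it defines subgroups by sex and matches an avatar to it.

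At stake are a small amount of power in each of the 11 comparisons, and agreement between the design, the model and the efficiency remark in the Sample size section.

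**Working it through.** **Inputs from the protocol article (Sample size).** Control rate: "we assumed that 38% of the control group will retest for HIV within 6 months". Size: "With a sample size of at least 3000 participants/arm". Intervention rate 38 + 4.7 = 42.7%. Alpha 0.00455; sidedness is not stated.

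**Step 1. Reproduce the planned figure with no covariate.** The two-proportion formula with pooled variance under the null is

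n = [z(α/2)·√(2p̄(1−p̄)) + z(β)·√(p₁(1−p₁) + p₂(1−p₂))]² / (p₂−p₁)².

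- p̄ = (0.38 + 0.427)/2 = 0.4035
- √(2 × 0.4035 × 0.5965) = 0.6938
- √(0.38 × 0.62 + 0.427 × 0.573) = 0.6930
- z(α/2) = 2.837 and z(β) = 0.842
- n = (2.837 × 0.6938 + 0.842 × 0.6930)² / 0.047² ≈ 2948 per arm

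At 3000 per arm, power for 4.7 points is 80.9%, and the detectable difference at 80% power is 4.66 points, which rounds to 4.7. A one-sided test would give 86.5% power, so the plan's figure is two-sided. No covariate adjustment is needed to obtain it.

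**Step 2. What sex could add.** On the risk-difference scale, adjustment multiplies the variance by (1 − R²), which is equivalent to an effective size of 3000/(1 − R²). For sex, R² = f(1−f)g² / [p(1−p)], where f is the female share, g the gap in retesting between the sexes and p = 0.38. Both f and g are **assumptions**; the documents give neither. With f = 0.5 and p(1−p) = 0.38 × 0.62 = 0.2356:

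| Assumed gap g | R² | Detectable difference (points) | Power at 4.7 points |
|---|---|---|---|
| sex not in model | – | 4.66 | 80.9% |
| 5 points | 0.25 × 0.0025/0.2356 = 0.0027 | 4.65 | 81.0% |
| 10 points | 0.25 × 0.01/0.2356 = 0.0106 | 4.63 | 81.4% |
| 20 points | 0.25 × 0.04/0.2356 = 0.0424 | 4.56 | 83.0% |

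A female share of 60% or 70% gives almost the same results (4.56 to 4.57 points at a 20-point gap).

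**Step 3. Cross-check on the logistic scale.** The (1 − R²) rule is an approximation for risk differences. In logistic regression, adding a prognostic covariate changes the odds ratio from marginal to conditional. The standard error of the log odds ratio need not shrink, and the gain appears in the test statistic. A simulation therefore fitted the logistic models directly. It used two arms of 3000, eight sites, sex balanced between arms, 400 replicates and a treatment log odds ratio of 0.195, close to ln[(0.427/0.573)/(0.38/0.62)] = ln 1.216.

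| Assumed sex log odds ratio | Approximate gap (0.2356 × log OR) | Power, site only | Power, site + sex |
|---|---|---|---|
| 0.2 | 5 points | 82.0% | 82.0% |
| 0.4 | 9 points | 80.0% | 80.5% |
| 0.8 | 19 points | 78.8% | 80.8% |

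The simulation error of one power estimate is about √(0.8 × 0.2/400) = 2 points, but both models were fitted to the same data sets. At a log odds ratio of 0.8 the mean test statistic rose from 3.588 to 3.652, or 1.8%. This agrees with 1/√(1 − 0.0424) = 1.022, or 2.2%, from step 2.

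**The case against.** The strongest reply is that this is a condensed article, that a statistical analysis plan exists but is not shown, and that the article does not say that site is the only adjustment term. A fuller covariate list, the variance method and the reported effect measure can all sit there. That holds for further covariates and for the effect scale. It is weaker for sex, because the article spells out the model and includes the companion stratification factor.

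A reader might infer more than the documents support:

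- **That the sample size depends on covariates the model leaves out.** It does not. Step 1 reproduces 4.7 points unadjusted. The remark about covariates is an unquantified extra and names none.
- **That the expectation of detecting less than 4.7 points contradicts the stated model.** It does not. That expectation rests first on Benjamini-Hochberg, which the Statistical analysis section specifies, and site terms are themselves covariate adjustment. No named covariate was promised and then dropped.
- **That results will be on the wrong scale.** The article does not say odds ratios will be the reported measure. Planning in percentage points and fitting a logistic model is ordinary practice, and a risk difference can be derived from the same fit.
- **That false positives are at risk.** Omitting a balanced stratification factor errs in the cautious direction.

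The objection that the gain is small also stands in full, and it sets the weight of the point.

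**Conclusion.** The point holds in a limited form. Sex is a stratification factor and is absent from the primary model as written, so inference is slightly conservative if sex predicts retesting. Even an assumed 20-point gap between the sexes costs only 4.66 − 4.56 = 0.10 point of detectable difference and about 2 points of power; at 5 or 10 points the cost is at most 0.03 point. If retesting does not differ by sex, there is no loss. Neither the validity of the test nor the 4.7-point planning figure is in question. The case for acting is that the change is free and makes the model match the design.

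**What to change.** 1. In Statistical analysis, state the primary model as logistic regression of retesting on the 11 arm indicators with terms for site and sex, or for the 8 × 2 = 16 site-by-sex strata.
2. Add sex to the PrEP-referral model. Do not force it, or strata terms, into the seroconversion, linkage and ART models. The article already concedes low power for HIV positivity and linkage, and with few events extra terms risk unstable estimates.
3. In Sample size, tie the remark on covariate adjustment to the covariates actually in the model, namely site and sex.
4. Optionally, report a standardised risk difference with its confidence interval from the same model, so that results can be read against the percentage-point target.

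The cost is a sentence or two. Sex is known before randomisation, so no new data are needed. Recruitment is expected to run to June 2027 and the statistician is to stay blinded through the primary analysis, so a model fixed now is still properly prespecified. If the unseen analysis plan already includes sex, only the article's wording needs aligning.

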**Fig. 1 Fig1:**
[figure not shown]
Schematic for the IBIS megastudy of interventions to promote HIV retesting among adults at increased risk of HIV infection in western Kenya and southwestern Uganda

The specific message content and framing will differ based on the participant’s randomization assignment. For example, participants who have been assigned to the “HIV risk assessment” study arm will be shown a video that asks them to reflect on several specific HIV risk factors and whether they have recently engaged in any of those activities, before prompting them to return for another test. Nine of the 10 messaging arms will have the same default avatar face for consistency. Based on feedback from the local adaptation phase, a male avatar of approximately 30 years of age was selected as the default. The “social norms (matched avatar)” study arm will use an avatar face that is matched to the participant’s age (≤ 30 years/> 30 years) and sex (male/female); the message content will be the same as that for the “social norms (default avatar)” study arm.

Participants who have been assigned to one of the 10 messaging arms will also receive brief SMS follow-up messages at 8 weeks and 11 weeks after their baseline visit, reminding them to return for HIV retesting in the 3–6-month window post-enrollment. The content of these SMS messages will also be aligned with the core content categories to which participants are assigned.

Participants who are assigned to the financial incentive study arm will be told by their HIV test counselor at baseline that they will receive a small financial incentive (< US$5) if they return for another HIV test within 3 to 6 months; they will not be shown any video messaging or receive follow-up SMS reminders. Participants in all study arms, including the control, will receive standard of care HIV post-testing counseling from HIV test counselors.

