#### Participant timeline and procedures

Immediately following enrollment, participants will complete a brief baseline survey including questions on demographics and recent HIV risk factors. Following the baseline survey, they will be randomized to one of the 12 study arms and, if assigned to one of the 10 messaging intervention arms, they will be shown the associated baseline video message. The study software will be programmed to automatically show only the video message for the study arm to which the participant has been randomized, to reduce possible human error. All participants will be reminded to return for another HIV test 3 to 6 months after the baseline visit. Participants who return for a repeat HIV test at follow-up will receive standard HTS through the hospital or clinic and will complete a brief follow-up study survey to assess HIV risk factors since baseline enrollment. The study team will record HIV test results as well. Participants who have been assigned to the incentive arm and return for retesting at follow-up will receive a small financial incentive (up to $5 USD) at the time of retesting. The schedule of study enrollment, interventions, and assessments is detailed in Table 2. Participants may seek and receive any concomitant care during their participation in this trial.

**Table 2 Tab2:** SPIRIT figure: schedule of enrollment, allocation, interventions, and assessments in the IBIS megastudy

	Enrollment	Post-allocation		Close-out	Post-close out
Timepoint	Baseline	*t* + 8 weeks	*t* + 11 weeks	*t* + 12 weeks–*t* + 24 weeks	*t* + 25 weeks–*t* + 48 weeks
Enrollment:					
HIV testing*	X			X	
Eligibility screen	X				
Verbal consent	X				
Allocation	X				
Interventions:					
[Control arm]	X				
[Incentive arm]	X			X	
[Messaging arms, *n* = 10]	X	X	X		
Assessments:					
Questionnaire	X			X	
Post-follow up survey for non retesters**					X

^*^ HIV testing is conducted per Ministry of Health (MoH) standard of care and is not a study procedure; HIV test results will be documented on study case report forms (CRFs)

^**^ We will reach out to a small sample of participants who did not return for HIV retesting to see if they tested elsewhere and, if not, to ask about their reasons for not retesting

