#### Outcomes

The primary outcome will be HIV retesting at any study venue 3–6 months after the initial baseline HIV test. We will use either participant demographic information (such as name, phone number, birthdate) and/or national identification number or electronic medical record number (if available) at baseline and time of retesting to verify participant identity (using procedures we have used in prior studies [5, 40]) and measure HIV retesting.

The secondary outcome will be PrEP referral acceptance (i.e., willingness to be referred to the PrEP clinic) among participants who retest HIV-negative and are not taking PrEP at time of retesting. We will measure acceptance of referral to PrEP services at time of retesting. Other outcomes will include the proportion of persons who test HIV positive (i.e., seroconvert) among participants who retest for HIV, as well as linkage to care and ART-initiation among those who seroconvert.

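### The models for HIV seroconversion state no term for time between tests, so a group difference in return time would carry into the odds ratio, chiefly in the pooled risk-factor analysis

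*Protocol article*

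**What the plan says.** In Statistical analysis the protocol states: "We will conduct similar analyses with logistic regression models for the dependent outcomes of HIV seroconversion among participants who retest". The word similar points back to the PrEP model just before it, which has study-community fixed effects and a multiplicity adjustment. The same paragraph adds that "we will identify baseline characteristics that are associated with incident HIV infection using logistic regression models". Neither statement mentions the interval between tests, an offset or person-time. The paragraph also concedes that power is lacking to compare HIV-positivity and linkage between arms, and presents those results as descriptive.

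In Outcomes, seroconversion is neither primary nor secondary: "Other outcomes will include the proportion of persons who test HIV positive (i.e., seroconvert) among participants who retest for HIV". The second test is timed by the primary outcome, "HIV retesting at any study venue 3–6 months after the initial baseline HIV test". Table 2 gives the same window as weeks 12 to 24.

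The cues about when to return differ by arm (Table 1 and the text after Fig. 1):
- Participants in the ten messaging arms "will also receive brief SMS follow-up messages at 8 weeks and 11 weeks after their baseline visit".
- One of those arms is also given a default appointment date at baseline.
- Incentive-arm participants are paid if they return within the 3–6 month window, and "they will not be shown any video messaging or receive follow-up SMS reminders".
- Control is listed with standard post-test counselling only.

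Participant timeline and procedures says that all participants are reminded to come back at 3 to 6 months.

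**The concern.** A participant who retests at week 24 has had twice as long to acquire HIV as one who retests at week 12, yet the stated models code both simply as positive or negative. If one group returns later on average, it will show a higher proportion positive even when its incidence is the same.

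The exposed analysis is the search for baseline characteristics associated with new infection. Randomization does not balance return time across such characteristics, the analysis pools all retesters, and the protocol's caveat about power covers arm comparisons only. A characteristic of people who come back late could then look like a risk factor for infection. Between arms the same mechanism could operate if the interventions change when people return as well as whether they do.

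**Working it through.** **Inputs from the protocol.** Retest window of 12–24 weeks (Table 2). From Sample size: 3,000 per arm, 12 arms, 38% retesting in control, a detectable difference of 4.7 points and significance level 0.05/11 = 0.00455.

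**Assumptions.** The protocol gives no incidence and no distribution of return times. I take a constant incidence λ, the same in both groups, of 0.5–4 per 100 person-years, and mean intervals of 14–17 weeks against 18 weeks. Every infection between tests is taken to be detected at retest.

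**1. The plan's own figure.** Comparing 38% with 42.7% at 3,000 per arm and two-sided 0.00455 gives 80.9% power, which agrees with the stated 80%. That figure concerns retesting; there is none for seroconversion. It supplies retester numbers: 3,000 × 0.38 = 1,140 and 3,000 × 0.427 = 1,281.

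**2. Odds ratio at equal incidence.** The probability of a positive retest at t weeks is p(t) = 1 − exp(−λt/52). The odds are exp(λt/52) − 1, which is close to λt/52 when infection is rare. So the odds ratio is close to t₂/t₁, and a group's proportion positive depends almost only on its mean interval. At λ = 1 per 100 person-years:

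| Mean weeks, earlier vs later | p earlier | p later | Odds ratio (later vs earlier) |
|---|---|---|---|
| 17 vs 18 | 0.326% | 0.346% | 1.06 |
| 16 vs 18 | 0.307% | 0.346% | 1.13 |
| 15 vs 18 | 0.288% | 0.346% | 1.20 |
| 14 vs 18 | 0.269% | 0.346% | 1.29 |
| 12 vs 24 (whole group at each end) | 0.231% | 0.460% | 2.00 |

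These ratios barely move between 0.5 and 4 per 100 person-years. The input that matters is the difference in mean interval.

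**3. Between arms.** Expected positives among 1,281 retesters at 18 weeks are 2.2, 4.4, 8.8 and 17.6 at 0.5, 1, 2 and 4 per 100 person-years. The chance that the later arm looks significantly worse (upper tail of a two-sided 0.05 test, 2.5% with no shift), comparing 1,140 with 1,281 retesters over that range of incidence, is:
- 1-week difference: 2.8–3.6%
- 3-week difference: 3.7–7.1%
- 4-week difference: 4.2–9.8%

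These use a normal approximation, which is rough with so few events, and make no allowance for multiplicity.

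**4. Pooled risk-factor model.** With 12 × 3,000 = 36,000 enrolled and an assumed 42% retesting there are 15,120 retesters. Split them into two equal groups by a baseline characteristic unrelated to incidence:

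| Difference in mean interval | Incidence per 100 person-years | Expected infections | Odds ratio | Upper-tail rejection (2.5% with no shift) |
|---|---|---|---|---|
| 1 week (17 vs 18) | 0.5 / 1 / 2 | 25.4 / 50.8 / 101.4 | 1.06 | 3.5% / 4.0% / 4.7% |
| 3 weeks (15 vs 18) | 0.5 / 1 / 2 | 24.0 / 47.9 / 95.6 | 1.20 | 6.5% / 9.2% / 14.2% |

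**5. With the interval in the model.** Under a complementary log-log model, log(−log(1 − p)) = log λ + log t. With log t as offset, equal incidence gives a rate ratio of 1 whatever the return times.

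**The case against.** The case against has real weight.

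- **Timing.** A reader might infer that the arms do shift retest timing, so that an arm with early return would pass for a prevention effect. The protocol does not support this. It shows only that cues differ. The SMS messages point to the whole window, the incentive is payable across the same window, and every arm is told to return at 3–6 months. Nothing is documented about return time by baseline characteristic either. This objection stands, so the point is conditional.
- **Size.** A reader might also take the two-fold window as the size of the bias. That range is between individuals; bias needs a difference between group means, and an odds ratio of 2 would need one whole group at week 12 and the other at week 24. This stands too.
- **Outcome.** The listed outcome is a proportion among retesters. Logistic regression is valid for it, and fewer positives at an earlier retest is a true feature of yield. A negative test followed by a positive one also identifies a new infection without knowing the interval; only a rate needs it. This stands for the descriptive measure. It does not settle the risk-factor model, whose stated target is incident infection.
- **Importance.** Seroconversion is an other outcome, and the protocol already says that the arm comparison is underpowered. This stands for arms. The caveat does not reach the risk-factor analysis.
- **Level of detail.** The full analysis plan is not shown and may already include the interval, and adding log interval to the planned logistic model would give nearly the same answer for a rare outcome. That is fair. Still, the article names the model for both analyses and mentions no time term.

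**Conclusion.** The point holds in a conditional and minor form. As stated, the logistic models for new infection carry no interval between tests, although that interval can vary two-fold between participants. If mean return time differs between the groups compared, equal incidence gives an odds ratio away from 1, by roughly 6% to 29% for differences of 1 to 4 weeks around 18 weeks. In the pooled risk-factor model a 3-week difference would raise the chance of a false signal in that direction from 2.5% to 6.5–14%. Between arms the effect is small against the handful of expected positives.

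These sizes rest on assumed incidence, assumed mean intervals, an assumed 42% retesting and equal-sized groups; the odds ratios depend almost wholly on the intervals. The primary analysis of retesting is not touched.

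**What to change.** Keep the proportion positive among retesters, by arm and overall, as the descriptive measure of yield. Fit the risk-factor model, and any arm comparison to be read as incidence, by complementary log-log or Poisson regression with the log of the baseline-to-retest interval as offset. Report infections per 100 person-years and the median test interval by arm beside the raw proportions. If the team prefers to keep the logistic models, the results should be described as positivity at retest rather than incident infection.

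The cost is analysis wording. Both test dates are already needed to decide whether a retest falls in the window, and the protocol expects follow-up to run to December 2027, so the change can be specified before the data are complete. The downside is that the offset assumes a constant hazard within the interval. It also leaves untouched the separate fact that only people who return are observed.

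### The arm-versus-control logistic models planned for linkage to care and ART initiation will probably leave at least one arm, and possibly the control, without a finite odds ratio

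*Protocol article*

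**What the plan says.** The Statistical analysis section of the protocol article first sets out the primary model: logistic regression with one indicator per intervention arm, control as reference, site fixed effects, and the Benjamini-Hochberg procedure. The model for PrEP referral follows the same pattern, with community fixed effects and the same multiplicity adjustment. The section then announces "similar analyses with logistic regression models for the dependent outcomes of HIV seroconversion among participants who retest and linkage to HIV care", and the sentence continues to cover "linkage to HIV care and ART initiation among those who test HIV-positive".

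It also plans to report the proportions who link and who start ART among seroconverters. A caveat follows: "Although we will be underpowered to detect differences between study arms in HIV-positivity and linkage to care", these outcomes can still be described. The Outcomes section places seroconversion, linkage and ART initiation under other outcomes, below the primary and the secondary outcome. The article states no expected seroconversion rate, linkage proportion or number of cases, and no method for sparse data.

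**The concern.** Read as similar to the models before it, the linkage model has 11 arm terms, 7 community terms (eight sites) and an intercept, about 19 parameters. It is fitted only to people who both retest and have seroconverted. If most of them link, an arm may contain nobody unlinked, or nobody positive at all. In the first case the maximum-likelihood log odds ratio for that arm runs off to infinity; in the second it is undefined. If it happens in the control arm, no arm-versus-control odds ratio is finite.

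This differs from low power. Low power gives wide but finite intervals; separation gives no finite estimate, and Wald p-values then carry no information. Under the plan those p-values would still go through the multiplicity adjustment.

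The group is also formed after randomisation, first by retesting, which the interventions aim to change, and then by seroconversion. Even a finite odds ratio would not be a randomised comparison.

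**Working it through.** **The plan's own figure.** The only power statement is for the primary outcome: "we will have 80% power to detect a 4.7 percentage-point difference in HIV testing" at 3000 per arm, with 38% retesting under control and two-sided alpha 0.05/11 = 0.00455 (z = 2.838).

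Power = Φ{[0.047·√3000 − 2.838·√(2·0.4035·0.5965)] / √(0.38·0.62 + 0.427·0.573)} = Φ{(2.574 − 1.969)/0.693} = Φ(0.874) = 0.81.

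The figure is reproduced. It says nothing about linkage or ART initiation.

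**Inputs from the Sample size section.** Arm size: "with a range of 2500–3333 participants per arm in a 12-arm trial". Retesting: "we assumed that 38% of the control group will retest for HIV within 6 months". Testers at the sites: "a reported HIV positivity of ~ 2" per cent. That last figure is positivity among all adult testers, not seroconversion 3–6 months after a negative test, so it serves only as a high bound.

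**Assumptions.**
- 3000 per arm (36,000 in all).
- 40% retesting on average, a little above the control figure: 3000 × 0.40 = 1200 retesters per arm, 14,400 in all.
- Proportion positive s = 0.25%, 0.5%, 1% or 2%.
- Proportion linked (or starting ART) L = 80%, 90% or 95%.

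**Formula.** Cases per arm are taken as Poisson with mean m = 1200·s. An arm has no variation if all its cases link, none link, or it has no cases:

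P = exp(−m(1−L)) + exp(−mL) − exp(−m).

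The expected number of affected arms is 12P, and the chance of at least one is 1 − (1−P)^12. P is also the chance that the control arm is affected.

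Worked case, s = 1% and L = 90%: m = 12, so P = exp(−1.2) + exp(−10.8) − exp(−12) = 0.301; 12P = 3.6; 1 − 0.699^12 = 98.6%.

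| s | Cases in all (12m) | L | P (any given arm, so also control) | Affected arms of 12 | At least one arm affected |
|---|---|---|---|---|---|
| 0.25% | 36 | 80% | 59% | 7.1 | >99% |
| 0.25% | 36 | 90% | 76% | 9.1 | >99% |
| 0.25% | 36 | 95% | 87% | 10.4 | >99% |
| 0.5% | 72 | 80% | 31% | 3.7 | 98.8% |
| 0.5% | 72 | 90% | 55% | 6.6 | >99% |
| 0.5% | 72 | 95% | 74% | 8.9 | >99% |
| 1% | 144 | 80% | 9% | 1.1 | 68% |
| 1% | 144 | 90% | 30% | 3.6 | 98.6% |
| 1% | 144 | 95% | 55% | 6.6 | >99% |
| 2% | 288 | 80% | 0.8% | 0.1 | 9% |
| 2% | 288 | 90% | 9% | 1.1 | 68% |
| 2% | 288 | 95% | 30% | 3.6 | 98.6% |

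A simulation drawing cases from a binomial over the 14,400 retesters, spreading them over 12 equal arms and drawing linkage within arm, gives the same results.

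**A plain check.** At s = 0.5% and L = 90%, about 72 × 0.10 = 7 people are unlinked. Seven people cannot give variation in 12 arms.

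**Sensitivity to size.** With 38% retesting, s = 1% and L = 90%, the chance that all 12 arms vary is 0.3% at 2500 per arm and 1.9% at 3333 per arm.

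**Community terms.** With 14,400·s/8 cases per site, a given site has no variation with probability 41% (s = 0.5%, L = 90%) or 17% (s = 1%, L = 90%). This adds to the problem.

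**The case against.** The strongest reply is that the deciding rates are not in the document, that the section already concedes low power and plans simple proportions, and that sparse-data rules belong in a statistical analysis plan that is not shown. Penalised and exact logistic regression are also logistic models, and the parameter count is inferred from the word similar. Much of this stands: the size of the risk is conditional, and the unseen plan may deal with it. But the article commits to these models as well as the proportions. It does not make the proportions a fallback, and its caveat concerns detecting differences, not whether estimates exist.

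A reader might infer more than the documents support:

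- **That most arms will have no variation.** This holds at 0.5% positive or below with 90% linked, or at 1% with 95%. It does not hold at 1% with 90% (3.6 arms) or at 2% with any linkage up to 95%.
- **That the models cannot be fitted, or that every contrast is infinite.** Arms with variation keep finite odds ratios if the control varies. Contrasts between two intervention arms that both vary need not fail even if it does not. Penalised and exact methods work under separation.
- **That false discoveries follow.** Wald p-values under separation drift towards 1, so the harm to the Benjamini-Hochberg step is lost power.
- **That the seroconversion and baseline-predictor models fail too.** With 38% retesting and 2500–3333 per arm, the chance of any arm with no seroconversions is 2–10% at 0.5% positive and about 0.1% or less at 1%. It reaches 40–69% only at 0.25%. The baseline-predictor model is described without arm contrasts, and nothing here shows that it fails.

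**Conclusion.** The concern holds for linkage to care and ART initiation only. With 36,000 enrolled, 40% retesting, 0.25–1% positive and 90–95% linked, at least one arm has no finite ordinary odds ratio with probability 98% or more. The control arm is affected with probability about 30–87%, and then no arm-versus-control odds ratio is finite. The conclusion rests on assumed positivity and linkage: the probability of any affected arm is about 68% at 1% positive and 80% linked, and about 9% at 2% and 80%. Selection after randomisation is a further reason not to read these contrasts as intervention effects. Severity is minor, since these are other outcomes and neither the sample size nor any primary conclusion depends on them.

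**What to change.** Drop the arm-by-arm regression and tests for linkage and ART initiation. Report counts and proportions by arm and overall, each with an exact 95% confidence interval, and say that the denominator is formed after randomisation. If a model is still wanted, pre-specify Firth-penalised or exact logistic regression with arms pooled into control, any messaging and incentive, and keep it outside the Benjamini-Hochberg family. The seroconversion and baseline-predictor models need not change on this ground.

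The cost is wording, to be settled before unblinding. What is given up is arm-specific odds ratios for two minor outcomes, most of which could not be estimated reliably in any case.
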